**Methods:**

The *Brilhar e Transcender* (BeT) study is a status-neutral, peer-led, single-arm digital intervention study enrolling 150 young transgender women in Rio de Janeiro, Brazil. The intervention was pilot tested and refined using data from a formative phase. The BeT intervention takes place over 3 months, is delivered remotely via mobile phone and in person by peers, and comprises three components: (1) BeT sessions, (2) digital interactions, and (3) automated messages. Eligibility criteria include identifying as transgender women, being aged 18-24 years, speaking in Portuguese, and living in the Rio de Janeiro metropolitan area in Brazil. The primary outcomes are HIV incidence, pre-exposure prophylaxis uptake, linkage to HIV care, and viral suppression. Primary outcomes were assessed at baseline and quarterly for 12 months. Participants respond to interviewer-based surveys and receive tests for HIV and sexually transmitted infections.

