### Eligibility Criteria

Inclusion criteria are (1) having been assigned the male sex at birth and self-identifying as *travesti*, a transgender woman, or having a gender identity different from identities typically associated with the assigned sex at birth; (2) being aged between 18 and 24 years; (3) providing consent for study participation; (4) living in Rio de Janeiro or the greater metropolitan area; and (5) being sexually active. Additional criteria for HIV-negative individuals include (1) no current PrEP use, (2) PrEP indication per Brazilian standards of care, and (3) no PrEP contraindication. For participants living with HIV, additional inclusion criteria are (1) having a confirmed HIV diagnosis, (2) not currently using antiretroviral therapy (ART) or having a detectable viral load and treatment that is not linked to HIV care.

Exclusion criteria include participation in any HIV prevention or care intervention study in the last year, refusal to undergo HIV testing, or having any health condition that, in the opinion of the investigator, precludes participation in the study or may lead to harm to the participant.

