### Study Procedures and Measures

Table 1 describes the study procedures. Potential participants are recruited by a community education team, through word of mouth, and via referrals from enrolled participants. Recruitment also occurs at the HIV prevention services based at our site and at an on-site mobile legal unit that offers weekly access to free legal services for transgender people.

Participants have 5 in-person encounters at the National Institute of Infectious Diseases Evandro Chagas, Fiocruz, including a screening and enrollment visit followed by 4 quarterly visits (at weeks 12, 24, 36, and 48). The BeT intervention takes place between the enrollment visit and the 12-week visit and is completed within that time frame. Trained staff conduct interviewer-administered surveys to participants at all study visits.

At baseline, all participants respond to a screening questionnaire and demographic information, after signing the written informed consent form. Baseline and quarterly survey content build upon questionnaires previously developed and tested with transgender women in Brazil and in the United States, as described in Table 2. During follow-up visits, we will collect information on study outcomes: HIV incidence, PrEP uptake and adherence among HIV-negative participants, and linkage to HIV care and viral load suppression among those living with HIV. In addition, we will also collect data on implementation science outcomes: (1) maintenance (pre- and poststudy) for study coordination, feasibility (poststudy) for peer health navigators, and feasibility, acceptability, and appropriateness (poststudy) for study participants.

**Table 1 table1:** Measures of the *Brilhar e Transcender* study.

Measures		Time frame	Source
Demographics		Baseline	Grinsztejn et al [6]
Transitioning process		Baseline and quarterly	Grinsztejn et al [6]
Food insecurity		Baseline and quarterly	Adapted from the Food and Agriculture Organization of the United Nations [35]

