### The BeT Intervention

The 3-month BeT intervention comprises three components: (1) BeT sessions, (2) digital interactions, and (3) automatic messages (Figure 2). During the first BeT session, the participant works with a peer navigator to build a case management plan aimed at meeting HIV prevention and care goals, and getting other needs met to promote health and wellness (BeT plan). BeT sessions 1 and 3 are conducted in person at enrollment and week 12 visits, respectively. BeT session 2 is conducted remotely via a mobile phone. Participants select a preferred app (eg, WhatsApp or Facebook messenger) for communicating asynchronously with the peer navigator during BeT session 2. Asynchronous digital interactions with peer navigators occurs at least weekly for 3 months and can be more frequent based on participant needs. Digital interactions were not restricted to study participation or HIV prevention or care and can include social support, food basket provisions, and guidance on employment, self-care, and other supports. Finally, participants received weekly automatic messages with health information on HIV testing, prevention, and care.

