### Statistical Analysis

Statistical analysis will assess recruitment, baseline, and follow-up data and will describe the rapidity of enrollment of young transgender women, their demographic and risk characteristics, and participation as the percent intervention uptake (ie, the number of participants in the BeT intervention divided by the total number of individuals who were assessed for participation and were preliminarily eligible for the study). We will describe PrEP uptake and adherence and HIV care service linkage at intervention initiation and completion. For the primary endpoint, we will compare PrEP uptake and adherence and HIV care linkage between baseline and follow-up data (ie, before and after the intervention). Primary analyses will test the hypothesis that the odds of PrEP uptake and adherence and HIV care linkage will be higher post intervention relative to baseline data. We anticipate behavior change within 3 instead of 6 months because of our ability to more frequently interact with participants (3 months). In fact, we may achieve a greater dose response and intervention effect in a shorter amount of time because of the possibility for a higher number of encounters. At minimum, participants will engage with their digital navigator 4 to 5 times a week in the form of short digital encounters, and over the course of the intervention, participants will have 48 to 60 short digital encounters in total. We will use a pooled logistic model to estimate treatment effects on time to PrEP uptake and adherence and HIV care linkage.

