We will also assess outcomes comparing data from the external comparison group to the BeT intervention group. First, we will conduct sensitivity analyses to compare the demographics of our intervention group to those of the external comparison group. In the analysis, we will focus on comparisons between the BeT intervention group and the external comparison group on measures of PrEP and ART adherence and viral suppression. Primary analyses will involve intention-to-treat analysis without considering adherence to the BeT intervention. This analysis will be a comparison of initiators of PrEP and ART, and we shall adjust for baseline confounders related to age or race. We have chosen to compare initiators of PrEP or ART and not assess PrEP uptake because a comparison of initiators parallels intention-to-treat analysis in which assignment and initiation of the treatment strategies occur together at baseline, regardless of whether individuals continue on the strategies after baseline [52]. We will combine outcome estimates with the cost estimates of the intervention component to calculate cost per participant and roughly estimate costs per HIV infection averted or poor health outcomes based on cohort data being collected in Brazil on HIV incidence and care outcomes.

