## Discussion

The BeT study is a pivotal study that will evaluate a digital peer-led intervention for young transgender women in a LMIC such as Brazil. We anticipate that the BeT intervention will successfully improve HIV prevention and care outcomes among young transgender women. A linkage to prevention intervention is particularly important once oral PrEP is a public health policy in Brazil. Oral PrEP requires strong care linkage, engagement, and retention to reap the prevention benefits. Although oral PrEP has been implemented since 2017 in Brazil, only a small percentage of PrEP users are transgender women [57]. Ancillary services and systems navigation to such services related to PrEP are essential supports to ensure success on PrEP. Among young cis women in Africa, PrEP uptake was facilitated when offered as part of an integrated sexual reproductive health service [58]. Based on the findings of the formative phase [32], BeT intervention will be the first intervention tested to meet the needs of the transgender women population in LMICs and may be implemented in resource-constrained settings. We also expect stigma to be reduced over time as participants are engaged in a gender-affirming transgender-centered clinic where an antistigma campaign has been conducted.

The study has some limitations. First, the BeT intervention will not be tested in a randomized clinical trial. Owing to the heightened targeting of transgender people, randomizing BeT participants seemed unethical and impractical in our context. To address this issue, we will assess intervention effectiveness by monitoring changes in intervention outcomes before and after the intervention and comparing outcomes from our cohort to those in an external comparison group. Furthermore, our study will have a convenience sample and our results may not be applicable to all young transgender women. Our study also has some strengths. The study team has extensive experience in conducting transgender-related research. The Brazilian site has a successful history of engaging transgender women in relevant clinical studies owing to historical community engagement efforts that solidified the relationship with the local transgender population.

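### The pooled logistic model is said to estimate treatment effects on time to PrEP uptake and HIV care linkage, but the single-arm cohort has no untreated time at risk and no planned comparison supplies any

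*Protocol article*

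**What the plan says.** The first paragraph of Statistical Analysis states the primary hypothesis as a before-after comparison of odds. It then closes with a further commitment: "We will use a pooled logistic model to estimate treatment effects on time to PrEP uptake and adherence and HIV care linkage". That sentence names a model, a target (treatment effects) and a time-to-event outcome. It names no comparator.

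The design is described in the Abstract as a "peer-led, single-arm digital intervention study enrolling 150 young transgender women in Rio de Janeiro, Brazil". The Discussion confirms the absence of random allocation: "First, the BeT intervention will not be tested in a randomized clinical trial".

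Exposure starts at time zero for everyone. The BeT Intervention section says "BeT sessions 1 and 3 are conducted in person at enrollment and week 12 visits, respectively", and Study Procedures and Measures says "The BeT intervention takes place between the enrollment visit and the 12-week visit and is completed within that time frame". Follow-up visits are at weeks 12, 24, 36 and 48.

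The second paragraph of Statistical Analysis introduces an external comparison group. It focuses on PrEP and ART adherence and viral suppression, and states a deliberate restriction: "We have chosen to compare initiators of PrEP or ART and not assess PrEP uptake". Linkage is not named among the outcomes compared with that group.

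**The concern.** A pooled logistic model is a discrete-time hazard model. It yields a treatment effect only by contrasting treated with untreated person-intervals among people still at risk of the event. In this cohort, time to PrEP start or to linkage runs from enrollment, and BeT runs from the same moment for every participant.

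PrEP uptake and linkage to care are two of the four primary outcomes listed in the Abstract. An analyst following the sentence literally would either find that the treatment term cannot be estimated, or drop the interval terms and report the difference between weeks 0-12 and later weeks as the effect of BeT. The second course would present a time trend as evidence that the intervention works.

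**Working it through.** The article gives no event count, hazard ratio or power for this model, so there is no figure to reproduce. The check asks whether any untreated time at risk exists, and what the model returns without it.

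**1. Where could untreated time at risk come from?**

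| Candidate source | What the article says | Usable for time to uptake or linkage? |
|---|---|---|
| Concurrent control arm | Single-arm, not randomized (Abstract; Discussion) | No |
| Unexposed follow-up within the cohort | Session 1 is at enrollment for everyone (The BeT Intervention) | No |
| Time before enrollment | "Additional criteria for HIV-negative individuals include (1) no current PrEP use"; entrants living with HIV are selected as off ART, or as having a detectable viral load and not being linked (Eligibility Criteria) | No. Status at entry is fixed by selection, and no time at risk is observed before enrollment |
| Weeks 12-48, after the sessions end | Intervention completed by week 12 (Study Procedures and Measures) | No. Everyone has already been exposed, and the contrast coincides with time since enrollment |
| External group | Adherence and viral suppression among initiators; uptake expressly not assessed; linkage not listed (Statistical Analysis) | Uptake: no. Linkage: not planned |

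A group made up of people who have already started PrEP or ART also cannot supply time to starting.

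**2. What the model can estimate.** Let I1 to I4 indicate the four quarterly intervals and T indicate treatment:

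logit(hazard) = a1·I1 + a2·I2 + a3·I3 + a4·I4 + b·T

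- BeT cohort only, T = 1 throughout: T = I1 + I2 + I3 + I4 in every row. Five columns, rank 4; b is not estimable.
- T = 1 in weeks 0-12 and 0 afterwards: T = I1. Five columns, rank 4; b is again not estimable.
- Unexposed comparator rows added over the same intervals: five columns, rank 5; b is estimable, although a causal reading would still need control of confounding.

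These ranks were confirmed numerically on simulated person-interval data. The assumed hazards do not affect them.

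**3. What happens if the interval terms are dropped.** The on- versus post-intervention odds ratio can then be computed, but it need not equal 1 when BeT does nothing. Assume that each participant has a constant probability of starting in each quarter, that nothing changes at week 12, and that there is no dropout. Half the cohort has probability pH and half pL. These are illustrative assumptions; the article gives no such figures.

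- **pH = pL:** the same probability applies in every interval, so the odds ratio is 1.
- **pH = 0.5, pL = 0.1:** in weeks 0-12 the proportion starting is 0.30, odds 0.30/0.70 = 0.4286. In the later intervals the at-risk fractions are 0.700 + 0.530 + 0.427 = 1.657 and the events 0.170 + 0.103 + 0.0677 = 0.3407, odds 0.3407/1.3163 = 0.2588. Odds ratio 0.4286/0.2588 = 1.66.
- **pH = 0.8, pL = 0.1:** in weeks 0-12 the proportion starting is 0.45, odds 0.45/0.55 = 0.8182. Later at-risk fractions are 0.550 + 0.425 + 0.3685 = 1.3435 and events 0.125 + 0.0565 + 0.03965 = 0.22115, odds 0.22115/1.12235 = 0.1970. Odds ratio 0.8182/0.1970 = 4.15.

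So the coefficient can depart from 1 with no BeT effect, but only if participants differ in readiness.

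**The case against.** **The sentence is loose wording, and the analysis plan will settle the model terms.** A condensed article does leave covariates to the full plan. But this article states the target itself, and itself excludes the one comparator that could support it for uptake. More detail would not resolve that. The wording has to change, or the external comparison does.

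**Treatment might mean dose.** The same paragraph mentions dose response, and The BeT Intervention section lets contact frequency vary with participant need. A dose term varies between people and would not be collinear with the interval terms, so the rank result depends on the coding assumed. That much stands. The article does not say a dose term is planned, however. Such a term would be confounded by need, and it would not estimate BeT against no BeT.

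**The primary hypothesis does not rest on this model.** This stands. The hypothesis is stated as a before-after comparison of odds, and the pooled logistic model is never labeled primary. The Discussion is also open about the lack of randomization.

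**The external group covers more than it is credited with.** This stands in part. Adherence is expressly compared with that group. For linkage the article is silent rather than prohibitive; the express exclusion covers PrEP uptake alone.

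A reader might go further in three ways that the document does not support:

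- That early starters leaving the risk set must by itself produce a large ratio. With a constant hazard common to all participants the ratio is 1, and the article gives nothing from which to size the variation in readiness.
- That all 150 participants contribute four intervals each. Uptake concerns only HIV-negative participants and linkage only those living with HIV, people leave the risk set once the event occurs, and 15% attrition is expected.
- That time to adherence is meaningless. Dried blood spots are scheduled at each visit for PrEP users, so time to a first adherent level can be defined.

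**Conclusion.** The point holds for the two initiation outcomes. For time to PrEP uptake, a BeT effect is not identified: the cohort has no untreated time at risk, and the external comparison expressly leaves uptake out. For time to linkage, no planned contrast identifies an effect, which is a slightly weaker statement because linkage is unlisted rather than excluded. For adherence the objection is not made, since an external contrast among initiators is planned.

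The number of untreated person-intervals in the cohort is zero, whatever the size of the risk set. No size can be put on the bias of an on- versus post-intervention coefficient; the values 1, 1.66 and 4.15 only show how far it depends on assumed readiness. The non-estimability result assumes a treatment indicator that is constant or coded by period, with a separate term for each interval.

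Severity is moderate. The sentence is wrong as written and concerns outcomes named as primary. A reader might infer that the study's primary analysis therefore fails, but that does not follow from this point: the before-after hypothesis is stated separately, and the model remains valid as a description of when participants start PrEP or are linked.

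**What to change.** Remove the treatment-effect wording from the sentence and give the discrete-time model a descriptive role. Report, with 95% CIs, the cumulative probability by weeks 12, 24, 36 and 48 of:

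- PrEP start, among HIV-negative participants;
- linkage to care, among participants living with HIV.

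State that differences between intervals describe timing and are not effects of BeT. Keep comparative claims on adherence and viral suppression within the external-group analysis already described. Analyzing adherence as a repeated binary outcome with GEE, a method the article already uses elsewhere, is a reasonable option but not a required correction.

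The change costs only analysis wording; visits and data collection stay as they are. What the study gives up is an effect claim on time to uptake and linkage that its design cannot support. Pooling external person-time to rescue that claim is not recommended as the default. It would reverse the article's reasoned choice to compare initiators, and it would need uptake and linkage dates that the article does not show to be available.

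### The external comparison is limited to people who started PrEP or ART, a step BeT is meant to cause, so it is not intention-to-treat for BeT and is open to selection bias

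*Protocol article*

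**What the plan says.** The second part of Statistical Analysis in the protocol article sets up a comparison of BeT with an external group on "measures of PrEP and ART adherence and viral suppression".

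- Label: "Primary analyses will involve intention-to-treat analysis without considering adherence to the BeT intervention".
- Population and adjustment: "This analysis will be a comparison of initiators of PrEP and ART, and we shall adjust for baseline confounders related to age or race".
- Deliberate omission of uptake: "We have chosen to compare initiators of PrEP or ART and not assess PrEP uptake".
- Reason given: "a comparison of initiators parallels intention-to-treat analysis in which assignment and initiation of the treatment strategies occur together at baseline".

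Two other places bear on this. Earlier in the same section, the before-after plan reads: "Primary analyses will test the hypothesis that the odds of PrEP uptake and adherence and HIV care linkage will be higher post intervention". Under Eligibility Criteria, HIV-negative entrants must have "no current PrEP use", and entrants living with HIV must be "not currently using antiretroviral therapy (ART) or having a detectable viral load and treatment that is not linked to HIV care".

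**The concern.** The parallel between a comparison of initiators and intention-to-treat works when the strategies compared are the drugs themselves, so that starting the drug is the assignment. Here the strategies are BeT and no BeT. A BeT participant is assigned at enrolment, and whether she then starts PrEP or ART is a result of what follows. Dropping non-starters from both groups therefore selects on a post-assignment event, and the two sets of starters need not be alike even if the full groups were.

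The Discussion names two ways of making up for the lack of randomisation: before-after change and this external comparison. Only the second has a comparison group. Within Statistical Analysis it is also the only analysis that names viral suppression, which the Abstract lists as a primary outcome. The same paragraph goes on to combine outcome estimates with costs, so a biased contrast could carry into the cost figures.

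**Working it through.** The article gives no sample size, rate, effect or power for the external comparison, so there is no planned figure to reproduce. The check has a logical step and an illustrative step.

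**1. Is starting a post-assignment event?**
- No HIV-negative entrant is on PrEP at entry, so any start of PrEP comes at or after enrolment.
- Entrants living with HIV who are off ART can likewise start only at or after enrolment.
- The before-after hypothesis is that uptake and linkage rise after the intervention, and a pooled logistic model is planned for time to uptake and linkage.

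The plan thus treats starting as an outcome of BeT in one paragraph and as a baseline entry condition in the next. This step needs no assumed rates.

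**2. What can the restriction do to the estimate? (all rates assumed)**

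Suppose the full groups are alike at baseline, and nobody who would start without BeT fails to start with it.
- π0: share who would start either way. π1: share who start under BeT.
- aA: adherence of those who start either way, without BeT. g: their gain from BeT.
- aI: adherence under BeT of the extra starters.
- Non-starters count as not adherent.

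Formulas:
- BeT, share of everyone adherent: T = π0(aA + g) + (π1 − π0)aI
- Starters-only contrast: T/π1 − aA
- All-eligible contrast: T − π0·aA
- Distortion of the starters-only contrast relative to g: [(π1 − π0)/π1] × (aI − aA − g)

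Example with π0 = 50%, π1 = 90%, aA = 70%, aI = 50%, g = 5 points:
- T = 0.50 × 0.75 + 0.40 × 0.50 = 0.575
- Starters only: 0.575/0.90 − 0.70 = 0.639 − 0.700 = −6.1 points
- All eligible: 0.575 − 0.350 = +22.5 points
- Distortion: (0.40/0.90) × (0.50 − 0.70 − 0.05) = −11.1 points, and 5 − 11.1 = −6.1

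| Change to the example | Starters only | All eligible |
|---|---|---|
| none | −6.1 | +22.5 |
| π1 = 100% | −7.5 | +27.5 |
| g = 10 points | −3.3 | +25.0 |
| aI = 70% | +2.8 | +30.5 |
| π1 = 50% (equal starting) | +5.0 | +2.5 |

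The sign turns when (π1 − π0)(aA − aI) exceeds π0·g. In the example that is 0.40 × (aA − aI) > 0.025, so the extra starters must adhere more than 6.25 points less well than the others do without BeT.

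A grid held aA at 70% and took π0 of 30, 50 or 70%, π1 of 70, 90 or 100% (always above π0), aI of 40, 50 or 70%, and g of 0, 5 or 10 points. Over its 72 combinations the starters-only contrast runs from −21 to +8 points and the all-eligible contrast from +8 to +52. The latter is positive throughout because BeT raises starting in every combination.

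**3. Does adjusting for age and race help?**

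In a simulation (1,000,000 people per scenario), unmeasured motivation drove both starting and adhering, 41% of the external group started, and logistic regression in starters adjusted for age and race.

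| BeT starting | 41% | 61% | 79% | 98% |
|---|---|---|---|---|
| Odds ratio, no true effect on adherence | 1.01 | 0.87 | 0.77 | 0.66 |
| Odds ratio, true effect 1.22 | 1.18 | 1.02 | 0.90 | 0.78 |

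The first row is selection bias alone. With a true odds ratio of 1.49 the estimate is 1.08 at 79% starting and 0.92 at 98%. A motivation score adding about 1 to each log-odds per SD reproduces both rows to within about 0.01, without the age and race terms. That strength is an assumption.

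**The case against.** Several points against the concern stand.

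- **Not the main analysis.** The before-after comparison is tied to the primary endpoint and covers uptake and linkage. The external comparison is introduced as an addition, and its word primary can be read as primary within that comparison. A reader might infer that the trial cannot credit BeT for uptake at all; that is true only of this contrast.
- **Reversal is not established.** A reader might infer that the sign will flip. That needs BeT to raise starting and the extra starters to adhere less well. The documents give no rates for the external group. The pilot of 20, where all but one participant living with HIV became suppressed, shows no sign of poor outcomes in persuaded starters.
- **Different questions are not bias.** If 60% of starters adhere in both groups and 90% versus 50% start, the starters-only difference is 0 and the all-eligible difference is 0.90 × 0.60 − 0.50 × 0.60 = +24 points. Zero is the right answer to the narrower question. That gap shows what the restriction leaves out, not an error in the estimate.
- **Some starts may fall at enrolment.** The dried-blood-spot footnote to the schedule of events allows for PrEP being started at the current visit, baseline included. The criterion for participants living with HIV can also be read as admitting people already on ART with a detectable viral load. Neither makes starting the assignment: it remains something BeT is expected to change.
- **The covariate list may be longer elsewhere.** A reader might infer that nothing but age and race will be adjusted for. An article can leave the full list to the analysis plan, and the group demographics will be compared. No baseline list would make a starters-only analysis intention-to-treat for BeT.

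**Conclusion.** The concern holds for the external comparison. The intention-to-treat label and its rationale are wrong as written, because the strategy compared is BeT and starting PrEP or ART is one of its hypothesised effects. That follows from the article's own text.

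The size of any bias rests on assumptions. If BeT does not raise starting, or if the extra starters do as well under BeT as the others do, the selection bias described here vanishes. If BeT raises starting and the extra starters do worse, a real benefit can be masked or reversed: −6.1 points against a true gain of 5 in the worked example. The documents support that as a possibility only. They do not support a claim that the before-after analysis of uptake and linkage is compromised.

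**What to change.** - Make the main external comparison all enrolled BeT participants versus all external-group members who meet BeT's entry criteria, with a common time zero at eligibility or enrolment.
- Count non-starters as not on PrEP, not adherent or not suppressed, unless a measurement shows suppression. Include PrEP uptake as an outcome.
- Adjust or weight for the baseline covariates that both datasets hold.
- Keep the starters-only comparison as a secondary analysis, labelled as conditional on initiation and without the intention-to-treat term.
- If the external data hold starters only, remove the label and its rationale and state the selection limitation.

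The cost is more analysis work and some loss of precision from weighting. No new data on BeT participants are needed. The main version depends on the external group including people who did not start.
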